**Primary outcome measures**						

Pain intensity and Pain-related disability	Chronic Pain Grade questionnaire	X	X	X	X	X

**Secondary outcome measures**						

Mood	Hospital Anxiety and Depression Scale	X	X	X	X	X
Participation in activities	Utrecht Activities List	X	X	X	X	X
Life satisfaction	Life Satisfaction Questionnaire	X	X	X	X	X

**Pain coping and pain cognitions**						

Pain coping	Coping Strategy Questionnaire	X	X	X^I^		X^C^
	Pain Coping Inventory	X	X	X^I^		X^C^
Pain cognitions	Pain Cognition List	X	X	X^I^		X^C^

**Other measures**						

Demographic variables (age, gender, marital status, and education)		X				

SCI and pain characteristics		X				

Neuropathic pain treatment		X	X	X	X	X

Functional independence	Barthel Index	X				

Satisfaction with intervention	Questionnaire on satisfaction		X^I^		X^C^	

X: intenvention group and waiting list control group

X^I^:only intervention group

X^C^: only waiting list control group

#### Chronic Pain Grade questionnaire (CPG)

The CPG [27] is used to assess pain intensity and pain-related disability. Participants have to rate their pain intensity on a 0-10 Numeric Rating Scale (NRS) for average pain, worst pain, and current pain (pain intensity score), and the degree of pain interference with daily activities, work/household activities, and recreational/social activities (pain-related disability score). The internal consistency for the pain intensity score and the pain-related disability score in an SCI population is excellent (Cronbach's alpha 0.95 and 0.94, respectively) [13]. In this study, the CPG is slightly adjusted to ask for neuropathic pain in the past week instead of the past six months.

#### Hospital Anxiety and Depression Scale (HADS)

The HADS is a 14-item self-report measure, which is used for scoring mood. It contains two 7-item scales: one for anxiety and one for depression, both with a score range of 0-21. It is a valid and reliable measure and responsive to change [28]. Woolrich and colleagues report a good internal consistency within an outpatient population with SCI [29]: the Cronbach's alpha for the anxiety scale is 0.85 and for the depression scale 0.79.

#### Utrecht Activities List (UAL)

The UAL [30,31] is a Dutch adaptation of the Craig Handicap Assessment and Rating Technique (CHART) [32] and is used to assess participation in activities. The questionnaire assesses the time spent on activities such as paid work, study, housekeeping, voluntary work, hobbies, and sports in hours per week, and the number of contacts per week with family, friends and acquaintances, and neighbours.

#### Life Satisfaction Questionnaire (LiSat-9)

The LiSat-9 [33] is used to assess life satisfaction and consists of a global item 'life as a whole' and eight domain-specific items 'activities of daily living', 'leisure', 'vocational situation', 'financial situation', 'sexual life', 'partnership relationship', 'family life', and 'contacts with friends'. These nine variables are rated on a six point scale (very dissatisfying to very satisfying), with higher scores reflecting greater satisfaction. The internal consistency of the total score (average of all item scores) is good (Cronbach's alpha of 0.80) in a Dutch SCI population [34].

### Pain coping and pain cognitions

#### Coping Strategy Questionnaire (CSQ)

The Dutch version of the CSQ [35] is an adaptation of the CSQ developed by Rosenstiel and Keefe [36]. The main difference between the original CSQ and the Dutch adaptation is a different answering format. In the Dutch adaptation people mark 10 cm visual analogue scales with the end-points defined in the same way as on the original seven-point Likert scale, i.e., as 'never do' and 'always do' [35]. The CSQ consists of 44 items in eight subscales to assess the use of six different cognitive strategies ('Diverting Attention', 'Re-interpreting Pain Sensations', 'Coping Self-Statements', 'Ignoring Pain Sensations', 'Catastrophizing', and 'Praying/Hoping'), and one behavioural strategy ('Increasing Activity Level'). Participants also rate how effective they think they are in controlling and decreasing pain ('Perceived Effectiveness'). A high score on a particular subscale indicates a higher endorsement of the cognitive coping strategy. The internal consistency is satisfactory to good (Cronbach's alpha range from 0.67 to 0.81) and the stability is reasonable to good (stability coefficients with a time interval of eight weeks range from 0.45 to 0.86) [37].

#### Pain Coping Inventory (PCI)

The PCI consists of 33 items with a four-point Likert scale, from 1 (rarely or never) to 4 (very often). The following six scales are distinguished, divided in active pain coping dimensions: 'Pain Transformation', 'Distraction', 'Reducing Demands', and passive pain coping dimensions: 'Retreating', 'Worrying', and 'Resting', all of which are internally reliable [38]. The internal consistency for the six scales range from 0.62 to 0.79 [39].

#### Pain Cognition List (PCL-2003)

The PCL-2003 consists of 39 items. Each item presents a specific pain cognition statement, for example, 'My thoughts are always concentrated on the pain'. Items are scored on a five-point Likert scale, from 1 (totally disagree) to 5 (totally agree) [40]. The questionnaire consists of five subscales ('Catastrophizing', 'Restrictions', 'Optimism', 'Internal Control', and 'Reliance on health care'), with varying length (from 4 to 16 items) and internal consistency (Cronbach's alpha of .64 to .88 with an average of 0.75), and with correlations between subscales ranging from .00 to .45. Validity of these subscales is supported by the meaningful pattern of correlations with other relevant constructs [41]. The stability of the PCL-2003 is satisfactory with the Pearson correlation coefficients with a time interval of two weeks ranging between 0.51 ('Reliance on health care') and 0.73 ('Catastrophizing') with an average of 0.64 [41].

Two questionnaires will be used for assessing pain coping, because they cover partly different coping styles and are additional to each other. The PCI assesses passive coping styles (like 'Resting' and 'Retreating', for example 'Slowing down when in pain'), while the CSQ assesses active coping styles (like 'Increasing Activity Level', for example 'I leave my home going to do something, like going to the movies or go shopping') and other coping styles that the PCI does not assess ('Ignoring Pain Sensations', 'Coping Self-Statements', and 'Praying/Hoping'). There is an overlap in the subscale 'Catastrophizing' between the CSQ, PCI, and PCL, but the PCL assesses people's cognitions (like 'I think fate has hit me') instead of coping ('When I'm in pain, I worry all the time about whether the pain will end').

### Compliance

In order to conduct this trial in a uniform way in the four rehabilitation centres, a detailed course book and protocol for each session have been written and a one-day training for the trainers will be organized. One of the authors (MH) will monitor on a regular basis (attending two sessions of the intervention group and two sessions of the control group in each centre) whether the content of the intervention will be executed as intended in the four rehabilitation centres. Compliance will be assessed by recording the number of sessions attended.

Neuropathic pain treatments will be registered at all measurements by using a pre-coded list including common pharmacological treatments, physical methods (e.g., TENS), surgical interventions, psychological treatment, alternative treatment (e.g., acupuncture), and other treatments. Participants will be allowed to continue their current pain treatments, but will be asked to refrain, if possible, from starting, stopping, or changing pain treatment during the intervention.

### Power analysis

The power analysis is based on information from a previous cross-sectional study [13], in which a mean pain intensity score on the CPG of 64.7 (SD 17.0) was seen in the subgroup of patients with a pain intensity score of 40 or higher. A mean difference of 16 points (corresponding to a 25% reduction from score 65 to 49) on the pain intensity score of the CPG between the intervention group and the control group in favour of the intervention group is regarded as clinically relevant. A minimum of 24 persons is required for each arm of the trial (total of 48 persons) to achieve sufficient statistical power (alpha 0.05, beta 0.90, one-tailed test). Expecting a maximum dropout rate of 20%, we aim to include 60 persons.

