### Data analysis

This trial with repeated measurements nested in each patient will be used to evaluate differences in effect between the intervention group and the waiting list control group. Differences between groups, with 95% confidence intervals, will be calculated for the outcome measures: CPG, HADS, UAL, and LiSat-9, by random coefficient (multilevel) analyses. The effectiveness of the intervention will be tested by analysing differences between the intervention group and the waiting list control group in the course of outcomes over time (0, 3, and 6 months, respectively t1, t2, and t3). Further, the long-term (6, 9, and 12 months, respectively t3, t4, and t5) impact of the intervention will be analysed in participants randomised to the intervention group. The impact of demographic and lesion characteristics, pain cognitions and pain coping on the effectiveness of the intervention will be studied explorative by merging data from the intervention group (t1, t2, t3) and the waiting list group (t3, t4, t5). Both the impact of differences at baseline, and changes in pain cognitions and pain coping during and after the intervention will be post-hoc analysed. Factor rehabilitation centre will be controlled for in the effectiveness analyses, but post-hoc analyses of differences between rehabilitation centres will be analysed and combined with information on compliance and patient satisfaction to identify determinants of a successful intervention. Data will be analysed according to the intention-to-treat principle. SPSS statistical program for Windows (version 16.0) and the MLwiN program of the Centre for Multilevel Modelling, Institute of Education, University of London (version 2.02) will be used for the analyses. Significance level will be set at a p-value less than .05.

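### The 24 per arm in the power analysis does not follow from the stated one-tailed test; it matches a two-tailed test at 90% power, and beta is mislabelled

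*Protocol article*

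**What the plan says.** The Power analysis section of the protocol article prints every input to the calculation.

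- Spread: "a mean pain intensity score on the CPG of 64.7 (SD 17.0) was seen in the subgroup of patients" scoring 40 or higher, taken from an earlier cross-sectional study.
- Target difference: "A mean difference of 16 points (corresponding to a 25% reduction from score 65 to 49) on the pain intensity score of the CPG", in favour of the intervention.
- Result: "A minimum of 24 persons is required for each arm of the trial (total of 48 persons".
- Error rates and sidedness: "to achieve sufficient statistical power (alpha 0.05, beta 0.90, one-tailed test".
- Recruitment: "Expecting a maximum dropout rate of 20%, we aim to include 60 persons".

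The Data analysis section then says "Differences between groups, with 95% confidence intervals, will be calculated for the outcome measures: CPG, HADS, UAL, and LiSat-9", using random coefficient (multilevel) models, and "Significance level will be set at a p-value less than .05". It does not say whether the tests are one- or two-sided.

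**The concern.** The figure of 24 is presented as the minimum that the listed inputs require. A reader who repeats the calculation with a one-tailed test gets a smaller number, so at least one item in the bracket is not what produced the 24. The beta entry is also wrong as written. Beta is the type II error, and 0.90 would mean 10% power.

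What is at stake is the decision rule for the primary comparison, not the size of the trial. The word one-tailed appears only in the power paragraph. The Data analysis section is silent on sides and reports 95% intervals, which usually accompany a two-sided 0.05 test. If a one-tailed 0.05 rule were carried into the analysis, the chance of falsely declaring benefit would be 5% rather than 2.5%. A result could also be called significant while its 95% interval includes zero. If the article leaves the side unclear, the choice could be made after the data are seen.

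**Working it through.** **Inputs**, all from the Power analysis section: difference 16, SD 17.0, alpha 0.05, power 0.90 (printed as beta), 1:1 allocation, dropout 20%.

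**Formula** (normal approximation, two means): n per arm = 2 × (z_alpha + z_power)² × (SD/difference)². Here (17/16)² = 1.129 and z_power = 1.282.

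**Step 1. Reproduce the printed 24.** With a two-tailed test, z_alpha = 1.960:
2 × (1.960 + 1.282)² × 1.129 = 23.7, so 24 per arm and 48 in total. With dropout, 48/0.80 = 60. All three printed figures reproduce. The t-test requirement is 24.7, so 25 per arm.

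**Step 2. Use the inputs as stated.** With a one-tailed test, z_alpha = 1.645:
2 × (1.645 + 1.282)² × 1.129 = 19.3, so 20 per arm, or 21 by t test. That is 40 to 42 in total, and 50 to 53 after 20% dropout (40/0.80 = 50; 42/0.80 = 52.5, rounded up). The printed minimum is 3 to 4 per arm above this.

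**Step 3. Does rounding of the effect explain the gap?** The difference could be 25% of 64.7 = 16.175, or 64.7 − 49 = 15.7.

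| Difference | One-tailed, 90% power (normal; t) | Two-tailed, 90% power (normal; t) |
|---|---|---|
| 16 | 20; 21 | 24; 25 |
| 16.175 | 19; 20 | 24; 25 |
| 15.7 | 21; 21 | 25; 26 |

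No version of the effect brings the one-tailed figure to 24.

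**Step 4. Does another power explain it?** One-tailed with 95% power needs 25 per arm for a difference of 16, and 24 for 16.175 (normal approximation). The article states 0.90, not 0.95. Taken literally, beta 0.90 (power 0.10) gives 1 per arm, so that reading cannot be meant.

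**Step 5. Power at 24 per arm.** The standard error of the difference is 17 × √(2/24) = 4.9, and 16/4.907 = 3.26.

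- Two-tailed: 3.26 − 1.960 = 1.30, power 90.3% (t test 89.1%).
- One-tailed: 3.26 − 1.645 = 1.615, power 94.7% (t test 94.1%).

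**Step 6. Size of the zone where test and interval part.** For a simple two-sample t test with 46 degrees of freedom, the critical values are about 1.68 (one-tailed) and 2.01 (two-tailed). Multiplied by 4.9, these are about 8.2 and 9.9 points. An observed difference between them would be one-tailed significant with a 95% interval that includes zero. This is an illustration only, because the planned multilevel model will have a different standard error.

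**The case against.** The strongest reply is that nothing of substance changes. The discrepancy is on the safe side: 24 per arm exceeds the one-tailed requirement and still gives about 90% power two-tailed. The beta entry is an obvious label slip. All of this stands, and it is why the point is moderate.

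Three further objections limit how far the point can go.

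- A reader might infer that the article contradicts itself on sidedness. It does not. The Data analysis section names no side and does not make the interval the decision rule, and a 95% interval can be reported as an estimate beside a one-tailed test. The pairing is a mismatch. A separate analysis plan may also settle the side.
- A one-tailed test may be deliberate. The Aims of the study section expects pain intensity to fall, and the power paragraph sets a difference in one direction. That would explain the word one-tailed, but not the 24.
- It is tempting to say that a two-tailed calculation was certainly run. The match holds under the normal approximation; the t test gives 25. One-tailed 95% power also comes close. The two-tailed reading is the more plausible because it uses the stated 0.90 and reproduces 24, 48 and 60, but it remains an inference.

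What survives is that the complete printed inputs do not yield the printed result. That is an error in the text, not a detail left out of a condensed article.

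**Conclusion.** The power statement is wrong as written. Under the stated one-tailed test at alpha 0.05 and 90% power, the minimum is 20 to 21 per arm, not 24. The 24 fits two-tailed alpha 0.05 at 90% power by the normal approximation (89% by t test), and beta should read 0.10. The side of the primary test therefore rests on a single word that the sample size does not support.

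A reader might conclude that the trial is too small or that its target must change. The figures do not support that: power for the stated effect is 89–90% two-tailed and about 94% one-tailed, and 60 remains right for 48 completers at 20% dropout. These figures assume a single comparison of two means at SD 17.0, which is the article's planning basis, not the multilevel model that will be fitted.

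Severity is moderate. The gain is a correct power statement and a primary test whose side is fixed before the data are seen.

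**What to change.** In Power analysis, replace the bracket with: *two-tailed alpha 0.05, power 0.90 (beta 0.10)*, noting that this is by the normal approximation (89% by t test). In Data analysis, state: *two-sided p < .05*. This agrees with the 24, the 48, the 60 and the 95% intervals.

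If a one-tailed test was truly intended, say so in both sections and justify it. Restate the power at 24 per arm as about 94%, and report the matching interval (a 90% two-sided interval or a one-sided 95% bound).

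Either route costs a few words and no additional participants. It should be settled before the primary analysis.

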### Data analysis

This trial with repeated measurements nested in each patient will be used to evaluate differences in effect between the intervention group and the waiting list control group. Differences between groups, with 95% confidence intervals, will be calculated for the outcome measures: CPG, HADS, UAL, and LiSat-9, by random coefficient (multilevel) analyses. The effectiveness of the intervention will be tested by analysing differences between the intervention group and the waiting list control group in the course of outcomes over time (0, 3, and 6 months, respectively t1, t2, and t3). Further, the long-term (6, 9, and 12 months, respectively t3, t4, and t5) impact of the intervention will be analysed in participants randomised to the intervention group. The impact of demographic and lesion characteristics, pain cognitions and pain coping on the effectiveness of the intervention will be studied explorative by merging data from the intervention group (t1, t2, t3) and the waiting list group (t3, t4, t5). Both the impact of differences at baseline, and changes in pain cognitions and pain coping during and after the intervention will be post-hoc analysed. Factor rehabilitation centre will be controlled for in the effectiveness analyses, but post-hoc analyses of differences between rehabilitation centres will be analysed and combined with information on compliance and patient satisfaction to identify determinants of a successful intervention. Data will be analysed according to the intention-to-treat principle. SPSS statistical program for Windows (version 16.0) and the MLwiN program of the Centre for Multilevel Modelling, Institute of Education, University of London (version 2.02) will be used for the analyses. Significance level will be set at a p-value less than .05.

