### Participants and procedure

Physiatrists from the four rehabilitation centres select former patients from their centre meeting inclusion criteria 1, 2, and 3 (Table 1). The selected persons will be sent a questionnaire to determine if they meet the inclusion (4, 5, and 6) and exclusion (1) criteria. In an interview with the psychologist, who will conduct the programme, will be checked for the other exclusion criteria and will be asked for written consent before final inclusion in the CONECSI trial. Included participants will be randomised (stratified by rehabilitation centre) to the intervention group or the waiting list control group (Figure 1). Measurements will be performed in both groups before starting the programme or entering the control group (t1), at 3 (t2), 6 (t3), 9 (t4), and 12 months (t5) follow-up. The control group will be invited for the programme after the follow-up measurement at 6 months.

**Table 1 T1:** In-and exclusion criteria

Inclusion criteria
(1) SCI

(2) at least 18 years old

(3) at least one year after discharge from first inpatient SCI rehabilitation

(4) main pain type is neuropathic pain

(5) duration of neuropathic pain of at least six months

(6) pain intensity score in the previous week of at least 40 on the 0-100 numerical rating scale of the Chronic Pain Grade

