### Intervention

This multidisciplinary programme is developed for people with CNSCIP. The programme consists of ten sessions of three hours over a ten-week period and a comeback session three weeks after the tenth session. Each meeting will be supervised by a psychologist and physiotherapist (the trainers) from the local centre. There will be a maximum of ten participants per group. The programme comprises educational, cognitive, and behavioural elements targeted at coping with CNSCIP. At the first session, participants will receive a course book containing information on all sessions, reading texts, and homework assignments. All participants will have a buddy who will attend two sessions. The buddy is the partner, family member, or a good friend of the participant. The buddy will be asked to read the course material, to help (if necessary) with the homework assignments, and the participants can discuss the intervention with the buddy. The trainers will receive the same course book as the participants, but with an extended protocol for each session. Additional file 1: Appendix 1 gives an overview of the main contents of the 11 sessions.

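### Treatment is given in course groups in one arm only, but the stated model has no course-group level, so any within-group correlation makes the standard error of the primary effect too small

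*Protocol article*

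**What the plan says.** **Delivery.** Under Intervention: "There will be a maximum of ten participants per group", and "Each meeting will be supervised by a psychologist and physiotherapist (the trainers) from the local centre". The programme has ten three-hour sessions and one comeback session.

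**Allocation.** Under Participants and procedure: "Included participants will be randomised (stratified by rehabilitation centre) to the intervention group or the waiting list control group". In the same section: "The control group will be invited for the programme after the follow-up measurement at 6 months". Controls therefore belong to no course group over the period of the primary comparison.

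**Model.** Under Data analysis: "This trial with repeated measurements nested in each patient will be used to evaluate differences in effect", by random coefficient (multilevel) analysis over t1, t2 and t3, with 95% confidence intervals. Also: "Factor rehabilitation centre will be controlled for in the effectiveness analyses". No course-group level is named.

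**Sample size.** Under Power analysis: "A minimum of 24 persons is required for each arm of the trial (total of 48 persons", followed by an increase to 60 for dropout of up to 20%. No other inflation is described.

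**The concern.** People who go through 11 shared sessions with the same trainers and the same fellow participants may end up with correlated outcomes. If they do, the 24 evaluable participants in the intervention arm carry less information than 24 independent people, while the controls remain independent up to t3.

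The centre factor does not deal with this. A centre main effect removes what both arms of a centre share. A course-group effect exists in the treated arm only. With about one intervention group per centre it is centre-by-arm variation, which stays in the treatment contrast. A model without that term attributes the variation to independent patients and reports too narrow an interval.

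At stake are the width of the 95% confidence interval for the primary effect, the false-positive rate of its test and, more conditionally, the power.

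**Working it through.** **Inputs from the protocol.** Difference 16 points, SD 17.0, alpha 0.05 one-tailed, power 0.90 (the protocol labels it beta), 24 evaluable per arm, dropout 20% (Power analysis); four centres (Setting); at most ten per group (Intervention).

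**Assumptions.** The ICC is not given; 0.01 to 0.20 is used. Group size m = 6 comes from 24/4, taking one intervention group per centre. That is an inference from the monitoring plan under Compliance, "attending two sessions of the intervention group and two sessions of the control group in each centre"; it is not stated outright.

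**Step 1: the plan's own figure.** n per arm = 2(z_alpha + z_power)² × 17²/16².
- Two-sided: 2(1.960 + 1.282)² × 289/256 = 23.7, so 24 per arm and 48 in total; 48/0.8 = 60. This reproduces the plan.
- One-sided: 2(1.645 + 1.282)² × 289/256 = 19.3, so 20 per arm. This does not reproduce it.

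The figure of 24 is thus the two-sided independent-samples result and contains no allowance for clustering. Without clustering, 24 per arm gives power 0.903 two-sided and 0.947 one-sided.

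**Step 2: clustering in the intervention arm only.**
- Design effect in the treated arm: DE = 1 + (6 − 1) × ICC
- Inflation of the variance of the difference: (1 + DE)/2
- True SE = 17 × √(DE/24 + 1/24)
- Two-sided type I error = 2(1 − Φ(1.96/√inflation))
- Power = Φ(16/SE − z), with z = 1.96 (two-sided) or 1.645 (one-sided)

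| ICC | DE | Inflation | SE ratio | Type I error, two-sided | Power, two-sided | Power, one-sided |
|---|---|---|---|---|---|---|
| 0 | 1.00 | 1.000 | 1.00 | 5.0% | 0.903 | 0.947 |
| 0.01 | 1.05 | 1.025 | 1.01 | 5.3% | 0.896 | 0.942 |
| 0.05 | 1.25 | 1.125 | 1.06 | 6.5% | 0.867 | 0.923 |
| 0.10 | 1.50 | 1.250 | 1.12 | 8.0% | 0.830 | 0.898 |
| 0.20 | 2.00 | 1.500 | 1.22 | 11.0% | 0.759 | 0.845 |

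Power reaches exactly 0.90 at an ICC of 0.005 (two-sided) or 0.096 (one-sided). With notional groups of 10, the one-sided threshold drops to 0.054.

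**Step 3: does the centre factor rescue it?** This was simulated with 20,000 trials, four centres, 6 per arm per centre, centre as a fixed effect and the group effect left out of the model. True SE against model SE was 5.21 v 4.87, 5.49 v 4.83 and 6.04 v 4.76 at ICC 0.05, 0.10 and 0.20. The two-sided type I error was 6.6%, 8.3% and 11.8%. Controlling for centre does not remove the problem.

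**Step 4: power of an analysis that does model the groups.** Satterthwaite df = (DE + 1)²/(DE²/3 + 1/23), with 3 df from four groups and 23 from 24 controls. Power is from the noncentral t distribution with noncentrality 16/SE.

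| ICC | df | Power, two-sided | Power, one-sided |
|---|---|---|---|
| 0 | 10.6 | 0.84 | 0.92 |
| 0.01 | 10.2 | 0.83 | 0.91 |
| 0.05 | 9.0 | 0.78 | 0.88 |
| 0.10 | 7.9 | 0.72 | 0.84 |
| 0.20 | 6.5 | 0.62 | 0.77 |

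At ICC 0 the two-sided figure is already 0.84 instead of 0.90. That part of the loss is the price of estimating a variance from four groups; it is not caused by clustering.

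**The case against.** **Power.** A reader might infer that the stated 90% power is simply not what this design delivers. The protocol does not support that. It states a one-tailed test, on which 24 per arm starts at 0.947 and stays at about 0.90 up to an ICC of about 0.10 by normal approximation. The calculation above also uses a single post-treatment score, whereas the planned model uses baseline and repeated measurements. As an illustration, assume a baseline correlation of 0.5 (not in the protocol), so that baseline explains 0.25 × 289 = 72.25 of the variance and leaves 216.75, and leave the group variance unreduced. At ICC 0.10 the group variance is 28.9 and the variance of the difference is 216.75/24 + (216.75 + 5 × 28.9)/24 = 24.1. The SE is 4.91, and two-sided normal-approximation power is again about 0.90. This objection stands and makes the power claim conditional. It does not repair the standard error.

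**Unknown ICC.** At ICC 0.01 the type I error is 5.3%, which is trivial. This stands as to size. The direction holds for any positive value.

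**Condensed article.** Random terms and degrees of freedom are often left to a fuller document. That stands for the degrees of freedom. But the article does state the nesting, the centre adjustment and the sample size, and the hierarchy it states lacks a level that the design creates.

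**Two other overreadings.** A reader might say that patients are the only structure modelled; centre is in fact controlled for. A reader might also apply the design effect to both arms; before t3 that would overstate the loss, because controls are not in groups.

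**Fragile remedy.** A variance from about four groups is imprecise and may be estimated at zero. This stands as a cost.

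**Conclusion.** The point holds for the standard error. The hierarchy as written omits a course-group effect confined to the treated arm, and the centre factor does not replace it. With four groups of 6, the reported SE should be multiplied by about 1.01, 1.06, 1.12 or 1.22 at ICC 0.01, 0.05, 0.10 or 0.20, so a nominal 5% two-sided test would reject about 5.3% to 11% of the time under the null.

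For power the conclusion is conditional on sidedness, on the ICC and on how much baseline and repeated measurements recover. The sample size contains no clustering allowance, but this alone does not show that the trial falls short of 90%. The mismatch between the one-tailed label and the figure of 24 is a separate matter, relevant here only because it decides which power column applies.

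The sizes rest on an assumed ICC and on one intervention group per centre. The direction rests on neither, provided that the ICC is positive. This should be changed before analysis.

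**What to change.** - **Data analysis, primary comparison:** add a random course-group effect for the intervention arm, with each control treated as a singleton, and use small-sample degrees of freedom for the treatment effect.
- **Data analysis, merged exploratory analysis:** include the course-group level for both arms, since controls are also treated in groups after t3.
- **Power analysis:** state power over an assumed ICC range, for example 0.01 to 0.10, for the sidedness that will actually be used, and say whether baseline and repeated measurements are counted.

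The cost is one extra term in multilevel software that is already planned, wider intervals, a somewhat less favourable power statement, and a group variance imprecisely estimated from about four groups. No extra patients are needed.

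### The effectiveness comparison lists pre-treatment t1 among the responses and names no baseline adjustment; if the t1 group means are left free, precision is given up that could be had at no cost

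*Protocol article*

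**What the plan says.** Under Data analysis, the protocol article estimates group differences for CPG, HADS, UAL and LiSat-9 "by random coefficient (multilevel) analyses". Effectiveness is the difference between intervention and waiting list "in the course of outcomes over time (0, 3, and 6 months, respectively t1, t2, and t3"). Participants and procedure places t1 before the programme starts or the control period begins, so t1 is a pre-treatment measurement.

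The only adjustment named for the effectiveness analyses is rehabilitation centre. Baseline differences are mentioned only in connection with the post-hoc work on cognitions and coping. The article does not say whether the t1 group means are free or constrained to be equal.

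The sample size (Power analysis) rests on a cross-sectional SD: "a mean pain intensity score on the CPG of 64.7 (SD 17.0") with a score of 40 or higher. The target is "A mean difference of 16 points", the settings are "alpha 0.05, beta 0.90, one-tailed test", and the result is "A minimum of 24 persons is required for each arm of the trial (total of 48 persons"). No credit is taken for the baseline measurement.

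**The concern.** A comparison of courses that starts at t1 is ordinarily fitted with group, time and group-by-time terms, and with a separate t1 mean for each group. The treatment effect is then a difference in change from t1, and any chance difference between the arms at t1 carries into the estimate. Under randomisation the two t1 means are equal in expectation. A model that uses this, either with t1 as a covariate or with a common t1 mean, estimates the same effect with smaller variance whenever the regression slope of follow-up on baseline is below 1.

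What is at stake is precision in a trial planned for 48 completers. Bias and type I error are not at issue.

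**Working it through.** **Inputs from the article.** Difference 16, SD 17.0, alpha 0.05, 90% power (the article writes this as beta), 24 per arm, 20% dropout, 60 in total.

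**Assumed.** The correlation rho between t1 and follow-up is not in the document, so 0.3 to 0.8 is shown. The main table takes SD 17 at every visit and the same correlation between all visits.

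**The plan's own figure.** n per arm = 2 × [17 × (z_alpha + z_power)/16]².
- Two-sided: 2 × [17 × (1.960 + 1.282)/16]² = 23.7, so 24. This reproduces the article's figure.
- One-sided, as the article words it: 2 × [17 × (1.645 + 1.282)/16]² = 19.3, so 20.
- Dropout: 48/0.80 = 60, which reproduces.

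The mismatch in sidedness is a separate matter, so both versions of power are shown below.

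**Formulas for the 6-month difference, 24 per arm.**
- Follow-up only: SE = 17 × √(2/24) = 4.91.
- t1 as a response with free group means: SE = 4.91 × √[2(1 − rho)].
- t1 as a covariate, or t1 as a response with equal means: SE = 4.91 × √(1 − rho²).
- Ratio of adjusted to free variance: (1 − rho²)/[2(1 − rho)] = (1 + rho)/2.

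A generalised least squares calculation for three visits gave the same SEs as these formulas. A linear slope with a free group intercept gave the same SEs as the free model with categorical time.

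| rho (assumed) | SE, free t1 means | SE, adjusted | Variance removed | Two-sided power at 16, free / adjusted | One-sided power, free / adjusted |
|---|---|---|---|---|---|
| 0.3 | 5.81 | 4.68 | 35% | 0.786 / 0.928 | 0.866 / 0.962 |
| 0.4 | 5.38 | 4.50 | 30% | 0.845 / 0.945 | 0.908 / 0.972 |
| 0.5 | 4.91 | 4.25 | 25% | 0.903 / 0.964 | 0.947 / 0.983 |
| 0.7 | 3.80 | 3.50 | 15% | 0.988 / 0.995 | 0.995 / 0.998 |
| 0.8 | 3.10 | 2.94 | 10% | 0.999 / 1.000 | 1.000 / 1.000 |

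Power is by normal approximation. If the effect is averaged over t2 and t3, the ratio becomes (1 + 2·rho)/3, that is 0.67 at rho 0.5 and 0.80 at rho 0.7.

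**If t1 is itself the score truncated at 40.** Baseline then varies less than follow-up and the formulas above do not apply. Selecting on t1 leaves the regression slope b and the residual variance unchanged, so:
- change variance = (1 − b)² × Var(t1) + residual variance;
- adjusted variance = residual variance;
- follow-up-only variance = b² × Var(t1) + residual variance.

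As an illustration, assume an unselected SD of 24 and a selected baseline variance of about 300 (SD about 17.3).
- Unselected correlation 0.5: b = 0.5 and residual variance = 576 × 0.75 = 432. Change variance = 0.25 × 300 + 432 = 507. The ratio to adjusted is 507/432 = 1.17, so adjustment removes about 15%. Follow-up only also has variance 507.
- Unselected correlation 0.6: b = 0.6 and residual variance = 576 × 0.64 = 369. Change variance = 0.16 × 300 + 369 = 417, a ratio of 1.13. Follow-up only has 0.36 × 300 + 369 = 477, so change is the more precise of those two.

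The gain from adjustment is smaller under truncation, but it remains.

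**The case against.** The strongest objection is that the article does not commit the fault. Its wording fits a model with t1 as a response and a common t1 mean, and in that model the SE equals the baseline-adjusted SE at every rho. The parameterisation of fixed effects is also the kind of detail that an article may leave to a fuller document. Both points stand, and they rule out the inference that placing t1 among the responses wastes precision by itself. What remains is that the article does state how t1 is used, names centre as the only adjustment, and gives no sign of the constraint. Free means are therefore the ordinary reading.

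A second inference is that entry at 40 or more lowers rho and so puts the trial where change scores do worst, below the precision assumed for the sample size. The documents do not support this. If t1 is the truncated score, truncation narrows the gap between the change and adjusted analyses, as shown in the working. The article leaves unclear whether the screening score and t1 are the same measurement. If they are separate, the equal-SD formulas may hold, but rho is still unknown.

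Third, the size is assumed and may be trivial. At rho 0.7 the two-sided power for 16 points is 0.988 against 0.995. Under the one-tailed test as worded, the free-means contrast still reaches 0.908 at rho 0.4. This stands as a limit on the point. So does the remark that sensitivity to chance baseline imbalance is the same variance loss described in another way.

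**Conclusion.** This is an efficiency gain available at no cost, and the planned analysis is not in error. A reader might infer that the group-by-time test is biased or invalid; it is neither, since randomisation keeps the change contrast unbiased.

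If the t1 means are free and the SDs are equal, adjustment removes about 10% of the variance (rho 0.8) to 35% (rho 0.3). In the truncation illustrations the saving is about 12% to 15% (1 − 1/1.13 and 1 − 1/1.17). If the t1 means are already constrained equal, there is nothing to gain. For the 16-point target the power gain matters at low rho and is negligible at high rho.

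The conclusion rests on an assumed rho, on the ordinary reading of an unstated model, and on t1 being unaffected by allocation.

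**What to change.** Add one sentence under Data analysis, applying to CPG, HADS, UAL and LiSat-9. Either of these will do:
- t2 and t3 are the responses, with the t1 score and rehabilitation centre as covariates; or
- t1, t2 and t3 are the responses, with the t1 mean constrained to be equal across arms and centre as a covariate.

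If the second model is already intended, the sentence only records it. The cost is wording alone: the t1 scores are already collected and the named software can fit either model. No change to the sample size is needed.
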